### Study Sample

A total of 250 residents will be recruited over 6 months among the 300 older residents currently in foster families. The primary end point will be the hospitalization rate at 12 months. A 30% hospital admission rate over a year has been reported in the Incidence of pNeumonia and related ConseqUences in nursing home Resident study in nursing home residents [16]. A change in the hospitalization rate from 30% to 15% would be considered as significant from a clinical and public health point of view. For an risk of 5% and 250 participants, the expected CI will be 4.4% for a hospitalization rate of 15% and 5.7% for a 30% rate.

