**Methods:**

This study cohort will include 250 older people living in foster families in Guadeloupe (French West Indies), as well as their respective foster caregivers. Both older people and caregivers will be interviewed concurrently on site at three time points: (1) at baseline, (2) at 6 months, and (3) at 12 months. For older people, we will collect anthropometric measures, cognitive impairment, depressive and anxiety symptoms, functional abilities, physical frailty, information on general health status, quality of life, and care pathways (hospitalization, mortality, and medical and paramedical consultations). We will also assess the quality of life and burnout symptoms of family caregivers at each follow-up. A phone update of vital status (alive or death) and care pathways of residents will be carried out at 3 and 9 months after the baseline examination.

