Despite strong family support, living at home is sometimes difficult or impossible for seniors and their caregivers [3] (heavy dependency, exhaustion of caregivers, regular decompensation of chronic pathologies, etc). Moreover, social isolation, social vulnerability, and loneliness among older people living at home [4,5] increase the risk of adverse health events, notably mortality [6]. The most developed and successful model for dependent persons in high- and middle-income countries is the nursing homes. However, the transition from one’s home to a nursing home usually disrupts residents’ social life and lifestyle, and institutionalized older people experience a steeper cognitive decline than community-dwelling people [7], as well as a drop in quality of life [8] and an increase in psychotropic drug use [9]. For these reasons, we need to study alternative and transitional care models between home care and nursing home care, such as foster families. Because fostered older people (while still moving out of their own homes) are taken care of within a family context instead of a nursing home or other collective settings, foster care placement processes could be an alternative to institutionalization. This model has developed to a greater extent over the last few years in Guadeloupe. Nearly 200 foster families care for about 300 dependent older people, whereas there are 21 nursing homes for approximately 1500 residents. Foster caregivers, after getting official approval and attending a 20-hour training course, usually accommodate 1 to 3 people in exchange for a monthly fee. Their mission is to ensure the well-being of their residents and to enable them to maintain close social and family relationships. Other professionals may also provide additional nursing care if necessary. Little is known about the characteristics of foster caregivers and their residents. Two decades ago, a study from Cébula and Horel [10] showed that 61% of fostered older people were older than 80 years in France, and two-thirds were women. Every 6 of 10 older people lived at home or with their own family before entering foster care, and foster care was requested by the older person’s household in 63% of cases. Most foster caregivers were women (96%). Two-thirds of the foster caregivers were between 40 and 60 years old, and 16% of them were older than 60 years. Every 8 of 10 foster caregivers were “partnered people,” the majority of them being single-family home owners (95%). Nearly half of the foster caregivers were in a nonemployment situation (inactive, unemployed, integration, and training) before obtaining their foster caregiver license. The cost of foster family accommodation for seniors depends on the number of caregiving hours, because of the length and frequency of stay (in 94% of cases, it is a full time) and geographical location. The monthly fee includes rent, services rendered, a maintenance allowance, and a daily allowance. Monthly cost ranges from €1400 to €2100 (US $1521.98 to US $2282.97) per month [11].

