To date, we do not know whether foster care is an alternative to nursing home care, as suggested by the limited existing literature, or a transitional care setting between home care and nursing home care. Epidemiological and medicoeconomic data on older people in foster families are essential to assess the relevance of this type of care, in particular, according to the severity of dementia or the degree of dependence in ADLs. Several issues need to be clarified: what is the residents’ annual hospitalization rate and the associated costs? What is the health care pathway of residents in terms of consultations with general practitioners, specialists, and paramedics? What is the prevalence of geriatric syndromes in this population, and the incidence of mortality? What is the incidence of pneumonia, the leading cause of death and emergency hospitalization in older people? What is the quality of life of the residents and their foster caregivers? The Karukera Study of Ageing in Foster Families (KASAF) is a prospective cohort study, designed to investigate these questions. This longitudinal study will assess the health status and medical and economic data of 250 foster family residents and their foster caregivers over a year.

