## Results

Recruitment opened in September 2020 and ended in May 2021, with 109 older people recruited and 56 respective foster caregivers. The 1-year follow-up was ended in June 2022. Data analyses are ongoing, and the first results are expected to be published in May 2023.

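### The only precision stated for the hospitalization rate is for 250 residents; recruitment closed at 109, and the article neither restates the precision nor lists the shortfall as a limitation

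*Protocol article*

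**What the plan says.** The target appears three times. The Abstract (Methods) says "This study cohort will include 250 older people living in foster families in Guadeloupe". The Introduction says the study will "assess the health status and medical and economic data of 250 foster family residents and their foster caregivers over a year". The Study Sample section says "A total of 250 residents will be recruited over 6 months among the 300 older residents currently in foster families".

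The Study Sample section then takes a 30% annual admission rate from a nursing-home study as its reference, names a fall from 30% to 15% as the change that would matter, and closes with the precision statement. That statement opens "For an risk of 5% and 250 participants" and ends "the expected CI will be 4.4% for a hospitalization rate of 15% and 5.7% for a 30% rate". It does not say whether the figures are half-widths or full widths.

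The outcome of recruitment is in the Abstract (Results) and again in the Results section: recruitment ended in May 2021 "with 109 older people recruited and 56 respective foster caregivers", and follow-up ended in June 2022. The limitations paragraph in the Discussion names three things: no data from informal caregivers, costs restricted to hospitalization, and no randomized comparison with nursing homes. The sample size is not among them.

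**The concern.** The precision statement is the only quantitative justification of sample size in the article, and it concerns the primary end point. It rests on a number of residents that the article itself reports was not reached and, with recruitment closed, can no longer be reached. The planned and achieved numbers are both printed, but nothing connects them, so the only precision on the page belongs to a cohort more than twice the size of the real one.

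A reader who carries ±4.4 or ±5.7 points forward will expect a tighter primary result than the study can give. The Discussion also intends to compare hospitalization rates with the twin study in nursing homes, if the residents prove similar, and the same expectation would carry into that comparison. The unlabelled figures add a smaller risk: read as full widths, they would suggest precision twice as good again.

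**Working it through.** **Inputs**
- Rates of 15% and 30%, 5% risk, planned n = 250: Study Sample.
- About 300 residents in foster care: Introduction and Study Sample.
- Achieved n = 109 residents with 56 caregivers: Abstract (Results) and Results.
- Two-sided 95% interval: not stated, but confirmed by step 1.

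**Step 1. Reproduce the stated figures.** Wald half-width h = 1.96 × √(p(1 − p)/n), with n = 250:
- 15%: 1.96 × √(0.15 × 0.85/250) = 0.0443, or 4.4 points.
- 30%: 1.96 × √(0.30 × 0.70/250) = 0.0568, or 5.7 points.

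Both match, so the figures are half-widths. Other forms at n = 250 do not match the pair: one-sided gives 3.7 and 4.8, continuity-corrected 4.6 and 5.9, and a finite-population correction with N = 300 gives 1.8 and 2.3.

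**Step 2. Same formula at n = 109.**
- 15%: 1.96 × √(0.1275/109) = 0.0670, or 6.7 points.
- 30%: 1.96 × √(0.21/109) = 0.0860, or 8.6 points.
- Ratio to the stated values: √(250/109) = 1.51.

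| Rate | 95% interval, n = 250 | 95% interval, n = 109 |
|---|---|---|
| 15% | 10.6% to 19.4% | 8.3% to 21.7% |
| 30% | 24.3% to 35.7% | 21.4% to 38.6% |

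**Step 3. Does the choice of interval matter?** At n = 109:
- Wilson at exactly 15% and 30%: 9.5% to 22.9% and 22.2% to 39.2%.
- Clopper-Pearson for 16/109 and 33/109: 8.6% to 22.7% and 21.8% to 39.8%.
- Finite-population correction, N = 300: half-widths 5.4 and 6.9 points.
- One-sided: 5.6 and 7.2 points.

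Even the most favourable variant is wider than 4.4 and 5.7.

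**Step 4. Residents who share a family.** 109/56 = 1.95 residents per caregiver, treating each caregiver as one family of average size. The design effect is 1 + (1.95 − 1) × ICC. The article gives no ICC, so this is an assumed range:
- ICC 0.02: design effect 1.02; half-widths 6.8 and 8.7 points.
- ICC 0.20: design effect 1.19; half-widths 7.3 and 9.4 points.

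**Step 5. Can 15% and 30% still be told apart at 109?** The upper limit around 15% is 21.7% (Wald), 22.7% (Clopper-Pearson) or 22.9% (Wilson), all below 30%. The lower limit around 30% is 21.4%, 21.8% or 22.2%, all above 15%. With ICC 0.20 the Wald limits are 15 + 7.3 = 22.3% and 30 − 9.4 = 20.6%. Each interval still excludes the other rate.

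**Step 6. Size of the shortfall.** 109/250 = 44% of target. Coverage of the roughly 300 residents falls from 250/300 = 83% to 109/300 = 36%.

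**The case against.** The strongest reply is that nothing in the sentence is wrong. It is explicitly conditional on 250 participants, and both figures reproduce. A protocol article normally keeps its methods in the planned, future tense and reports recruitment under results. This one gives the 109 twice, and in the Abstract it comes straight after the 250. No sentence claims that the achieved precision is 4.4 or 5.7 points. The study is descriptive, with no test or power claim that fails at 109, and the Data Analysis section plans a 95% interval for the mean number of hospitalizations, which will reflect the real sample size whatever was anticipated.

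Most of this stands. A reader might infer a calculation error, a hidden shortfall, or a claim that 250-resident precision was achieved. The article supports none of these.

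A reader might also note that the two Wald intervals at 109 just overlap (21.7% against 21.4%), whereas at 250 they are about 5 points apart, and conclude that the study can no longer tell 15% from 30%. That does not follow. The study will produce one estimate, to be read against a reference rate, and step 5 shows that an interval around either rate excludes the other.

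What the reply does not answer is the gap between the two numbers. The article was written with recruitment and follow-up closed, prints a precision for one size and an enrolment of another, and has a limitations paragraph in which the difference would belong. This is not detail that an article leaves to a fuller protocol or analysis plan, since both figures are in the article itself.

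**Conclusion.** The point holds as a reporting defect. The stated half-widths of 4.4 and 5.7 points are right for 250 residents but are not what a cohort of 109 delivers. For that cohort they are about 6.7 and 8.6 points, 1.51 times as wide, and nothing in the article says so.

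The 6.7 and 8.6 assume that all 109 recruited residents contribute to the 12-month rate, that residents are independent, and that the interval is a two-sided 95% Wald interval. Fewer analysable residents would widen the intervals. Clustering would too: about 7.3 and 9.4 points at an assumed ICC of 0.2 with 1.95 residents per caregiver. A finite-population correction would narrow them to 5.4 and 6.9, still wider than stated.

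The conclusion goes no further than lost precision. The design's own contrast of 15% against 30% remains resolvable at 109.

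**What to change.** Changes to the text:
1. In the Abstract, Introduction and Study Sample section, keep 250 as the original target and mark it as not met, with 109 residents and 56 caregivers recruited. The planned number should stay visible as the prior rationale.
2. In the Study Sample section, label 4.4 and 5.7 points as 95% half-widths for n = 250.
3. Add one sentence there: for the 109 residents recruited, the half-widths are about 6.7 points at a rate of 15% and 8.6 points at 30%, before any allowance for residents who share a foster family. If an allowance is shown, state the assumed ICC.
4. Add the shortfall to the limitations paragraph: 109 of 250 planned, about 36% rather than 83% of the roughly 300 residents.
5. Interpret the primary rate, and any comparison with the nursing-home twin study, against the restated precision.

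The cost is wording only. No new participants, data or change of design are needed. The stated precision becomes less favourable, which is an accurate description of the cohort as recruited.

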### Study Recruitment

#### Inclusion Criteria

To be eligible for the study, residents must be older than 60 years. They must live in a foster family in Guadeloupe and benefit from the French social security.

#### Exclusion Criteria

The only exclusion criterion is refusal from the resident or his or her legal guardian to participate in the study.

#### Preinclusion Visit

Before the start of inclusions, residents, their families, and the foster caregivers will be informed of the goals and methods of the KASAF via information meetings and emailing campaigns.

The on-site investigator will screen for eligible participants among the residents of the foster family he or she is responsible for and will visit every resident meeting the criteria. He or she will inform them of the aims of the study, the computerized processing of their personal data, the access to their data in the local PMSI (Program for Medicalization of Information Systems [Programme de médicalisation des systèmes d'information]) server, and their right to object to their participation at any given time. An information leaflet will be given to every participant and to the referring professional caregiver identified by the investigator to complete the interviews. Foster caregivers and residents have a right to oppose the collection of their personal data.

#### Data Collection

At inclusion, nurses, geriatricians, and psychologists will collect sociodemographic, health-related, and psychosocial information. The inclusion visit is the first on-site interview and will be followed by 4 visits: 2 on-site visits 6 and 12 months after the inclusion visit, and 2 phone interviews 3 and 9 months after the inclusion visit (Table 1).

The interviewers will be conducted by health care professionals: psychologists, interns, and nurses, trained by the INSERM Team SEPIA (UMR 1219) from the University of Bordeaux, a team having expertise in implementing cohort studies.

**Table 1 table1:** Expected timeline for the KASAF^a^.

Time line	Goal
July-September 2020	Ethics Committee approval Registration on ClinicalTrials.gov
September 2020	Training sessions for the interviewers
November 2020-May 2021	Inclusion period
February 2021-February 2022	3-, 6-, and 9-month follow-up
February 2022-May 2022	End of 12-month follow-up (end of data collection)
June 2022-March 2023	Data analysis
From May 2023	Scientific communications

^a^KASAF: Karukera Study of Ageing in Foster Families.

#### On-site Interviews

Participants will be interviewed at baseline, after 6 months, and after 12 months. At each visit, different function domains will be assessed to measure (1) the ability to perform ADLs (eg, personal care, eating, and mobility) and (2) the ability to perform instrumental ADLs (eg, using the telephone, shopping, and managing finances). In fact, the interview implies both a physical evaluation (grip strength, gait speed, and blood pressure) and a cognitive and a psychological assessment. The estimated time for completion is 30 minutes but may vary depending on the participant’s physical and cognitive status. Each of the participants will remain in the study for further follow-up interviews even if he or she is unable to answer, and reasons for incomplete data will be documented by the interviewers. Interviewers may split the visit into 2 parts to respect the participant’s rhythm and to avoid missing data.

During on-site visits, foster caregivers will provide their own sociodemographic data (as well as information on the caregiving burden borne) and those of the elders to be cared for. Thus, both the quality of life of foster caregivers and the main sociodemographic or health data of the participants (eg, medical history, medication, nutrition, and ADL/Instrumental Activities of Daily Living [IADL] performance) are the primary focus of the study.

#### Phone Interviews

Interviewers will phone the foster caregivers twice to collect data on participants 3 and 9 months after the first visit. This phone call will provide an update on the mortality status of foster elders and health care services (ie, types and frequency of use). In the event of the death of a participant, date and cause of death will be sought and documented whenever possible.

### Outcomes

Information on health care pathway comprises hospitalizations and consultations with general practitioners, specialists, and paramedics.

#### Primary Outcome

The main outcome is the number of hospitalizations over a year. The French hospital discharge database (PMSI) will provide information on hospital admissions. This information will be retrieved with the approval of the participants or their legal representative. Information on hospital admissions will also be collected from the foster caregiver for confirmation.

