### Data Analysis

First, the analysis will describe the number of included participants, the inclusion curve (evolution of the number of people included between the first and last inclusion), the number of theoretical visits, the number of visits actually made, and the ratio of both (number of visits made or number of theoretical visits).

A description of the rate and causes of death and study dropout will also be provided.

The following quantitative variables described in terms of number of staff, mean, and interindividual SD and 95% CI of the mean, median, range, and IQR values: number of hospitalizations, total length of hospitalization, total cost related to hospitalizations, total number of consultations with a general practitioner, total cost of low respiratory infections, total number of falls, MMSE score, total number of drugs, NPI score, QoL-AD score, SF-36 score, and Pro-QoL score.

Qualitative variables (ordinal: AGGIR grid, feeling of loneliness; dichotomous: vital status; presence or absence: frailty syndrome, depression, undernutrition, visual impairment, hearing impairment, incontinence, ADL dependency, IADL dependence) of participants at inclusion will be described in terms of frequency and number.

Comparisons between the 3 times (T0, T6, and T12) will be performed using repeated-measures ANOVA for quantitative variables and the Cochran-Armitage test for trend for qualitative variables.

Statistical analyses will be performed using the RStudio software (version 2.7; Posit Software).

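### The primary endpoint is sized as a percentage hospitalized but defined and summarised as a number of admissions

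*Protocol article*

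**What the plan says.** Three sections of the protocol article fix the primary endpoint, and they do not agree.

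- **Study Sample** names a rate: "The primary end point will be the hospitalization rate at 12 months". It takes a benchmark from a nursing home study ("A 30% hospital admission rate over a year has been reported"), sets a yardstick ("A change in the hospitalization rate from 30% to 15% would be considered as significant from a clinical and public health point of view"), and gives the precision: "the expected CI will be 4.4% for a hospitalization rate of 15% and 5.7% for a 30% rate". The Abstract and Objectives also speak of a rate.
- **Primary Outcome** names a count: "The main outcome is the number of hospitalizations over a year". The source is the hospital discharge database, with confirmation from the foster caregiver.
- **Data Analysis** puts the count in its list of quantitative variables, to be described by mean, SD, 95% confidence interval of the mean, median, range and IQR ("IQR values: number of hospitalizations, total length of hospitalization"). The list of qualitative variables, reported as frequencies, does not contain hospitalized yes/no.

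**The concern.** A percentage of residents hospitalized and a mean number of admissions per resident are different quantities, with different variances. If the study is sized on the first and reports the second, the precision promised in Study Sample describes something other than the result, and the 30% and 15% figures are no yardstick for it.

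The practical risk lies in reporting. With both definitions in print and the word rate covering either, the choice between them stays open after the data are seen, and the comparison with 30% can change with that choice. This touches the study's purpose: the Discussion plans to compare hospitalization rates with a twin study in nursing homes and to use the data to support resource allocation.

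**Working it through.** **Inputs from Study Sample.** N = 250 and a 5% risk ("risk of 5% and 250 participants"), rates of 15% and 30%, stated precision 4.4% and 5.7%. I take the 5% as two-sided, which the figures bear out.

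**Step 1. Reproduce the stated precision as a binomial proportion.** Half-width = 1.96 × √(p(1 − p)/n).

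- p = 0.15: 1.96 × √(0.15 × 0.85/250) = 1.96 × 0.02258 = 0.0443, or 4.43 points.
- p = 0.30: 1.96 × √(0.30 × 0.70/250) = 1.96 × 0.02898 = 0.0568, or 5.68 points.

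Both match. The stated figures are half-widths, not full widths.

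**Step 2. Try the other readings.**

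| Method, n = 250 | at 15% | at 30% |
|---|---|---|
| Stated in the article | 4.4 | 5.7 |
| Two-sided binomial, Wald | 4.43 | 5.68 |
| Two-sided binomial, Wilson | 4.42 | 5.65 |
| One-sided 5% binomial | 3.71 | 4.77 |
| Binomial with finite-population correction, 250 of 300 | 1.81 | 2.32 |
| Poisson mean count, per 100 residents | 4.80 | 6.79 |

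The Poisson row is 1.96 × √(m/250) with m = 0.15 and 0.30. With an assumed variance-to-mean ratio of 1.5 to 3 it widens to 5.9–8.3 and 8.3–11.8 per 100. Only the two-sided binomial readings fit, so the sizing used one yes/no value per resident.

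**Step 3. Relate the two quantities.** For a count N, the mean equals P(N ≥ 1) + P(N ≥ 2) + P(N ≥ 3) + … The first term is the proportion hospitalized and the rest are repeat admissions. The mean therefore equals the proportion only if nobody is admitted twice, and otherwise exceeds it. This needs no distributional assumption.

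**Step 4. Size of the gap.** The article gives no dispersion, so these are illustrations under assumed distributions.

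- Poisson: P(N ≥ 1) = 1 − exp(−m). Setting this to 0.30 gives m = −ln(0.70) = 0.357. Half-width of the mean at n = 250: 1.96 × √(0.357/250) = 0.074.
- Negative binomial with size k: P(N ≥ 1) = 1 − (1 + m/k)^(−k) and variance m + m²/k.

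| Assumed distribution | Mean count if 30% are hospitalized | Half-width of that mean, n = 250 | % hospitalized if the mean is 0.30 |
|---|---|---|---|
| Poisson | 0.36 | 0.074 | 25.9 |
| Negative binomial, k = 1 | 0.43 | 0.097 | 23.1 |
| Negative binomial, k = 0.5 | 0.52 | 0.128 | 20.9 |
| Negative binomial, k = 0.25 | 0.79 | 0.225 | 17.9 |

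A cohort exactly at 30% hospitalized would thus show 36 or more admissions per 100 residents. A cohort with 30 admissions per 100 residents would have at most about 26% hospitalized under these assumptions.

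**The case against.** The strongest reply is that this is loose wording in a condensed article about a descriptive study. Four parts of it stand and limit the point.

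- **No test depends on it.** The study is sized for precision, and Data Analysis plans no test of hospitalization against 30% or 15%. A reader might infer that the main conclusion is invalid. The documents do not support that; the exposure is misapplied precision and selective quotation of a rate.
- **The proportion is not lost.** A reader might infer that the study cannot or will not produce it. Data Analysis as written does not list it, but that section limits its qualitative list to participants at inclusion, and the full protocol and any SAP are not shown. The proportion can be derived from the admission data already planned.
- **The meaning of the cited 30% is not given.** The article never says hospitalized at least once. The binomial arithmetic shows how precision was computed, not what the source study measured. A reader might infer that the 30% is a percentage of residents, but it could be admissions per 100 residents.
- **The gap has no single size.** It depends on assumed dispersion. Setting 0.074 or 0.097 beside 0.057 might suggest a measured loss of precision. These are half-widths of different quantities, so they show only that the stated figure does not carry over.

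The reply does not remove the contradiction. Reading rate as admissions per 100 residents fails to reproduce 4.4 and 5.7, so the sizing and the defined outcome cannot both be the primary endpoint.

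**Conclusion.** The primary endpoint is stated inconsistently. Study Sample treats it as a 12-month percentage with binomial half-widths of 4.4 and 5.7 points at 250 residents. Primary Outcome defines it as a count, and Data Analysis as written summarises only that count. The stated precision does not apply to the mean count, and the 30% to 15% yardstick cannot be set against it unless the 30% is shown to be on the same scale.

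That much rests on the article's own text and arithmetic, plus the two-sided reading of the 5%. That the mean exceeds the proportion whenever anyone is readmitted is also assumption-free. The size is not: a mean of about 0.36 for 30% hospitalized assumes a Poisson count, and 0.43 to 0.79 assumes a negative binomial with k from 1 to 0.25. The fault lies in the definition of the endpoint and its listed analysis, not in data collection.

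**What to change.** 1. Use one primary endpoint in Study Sample, Primary Outcome and Data Analysis. The one that matches the sizing is the proportion of residents with at least one hospital admission within 12 months of inclusion, with its 95% confidence interval. Add it to Data Analysis.
2. State how residents who die before 12 months without an admission are counted. This is not a marginal detail: the Introduction cites 12-month mortality of 32.0% and 28.8% in a randomized comparison of foster care and nursing homes.
3. Make the number of admissions a secondary outcome, expressed per person-year so that shortened follow-up is allowed for.
4. State whether the cited 30% is a percentage of residents or admissions per 100 residents, and compare it only with the matching measure.

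Keeping the count as primary would also remove the contradiction, but the precision statement would then have to be redone with a stated dispersion.

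The cost is wording in three sections and one extra summary from data already planned. Follow-up ended in June 2022 and analysis is reported as under way, so the change should be recorded as a dated clarification before results are reported, noting whether hospitalization data had been examined by then.
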